## Abstract

Cerebral Palsy is one of the most prevalent motor disabilities in childhood, significantly impacting both children and their caregivers. This mixed-methods study explores the experiences, psychological well-being, and unmet needs of caregivers of children with Cerebral Palsy. Using an explanatory sequential design (QUAN → QUAL), first it will be assessed burden, stress levels, and quality of life of caregivers through standardized questionnaires (PedsQL-FIM, ZBI, PSS-14). In the second phase, semi-structured interviews will be conducted to provide a deeper understanding of these variables. Other studies indicate that caregivers experience heightened stress and decreased quality of life, influenced by their child’s functional limitations and the lack of adequate social and healthcare support. Moreover, many caregivers struggle with navigating medical systems, balancing personal and professional responsibilities, and managing emotional distress. This study will highlight the urgent need for family-centered interventions, psychosocial support, and healthcare policies that address not only the medical needs of children with Cerebral Palsy but also the well-being of their caregivers. By integrating quantitative and qualitative data, this research will provide comprehensive insights into the caregiving burden and will offer recommendations for improving caregiver support strategies. The Clinical Trial is registered at ClinicalTrials.org with the registration number NCT06912373.

## Introduction

Neurological disorders are characterized by impairments affecting various regions of the brain or nervous system and requires comprehensive, multidisciplinary approach to their management, particularly in paediatric populations [1,2]. Effective care for children with such conditions relies on a thorough understanding by healthcare professionals, caregivers, and parents [2,3].

Parents of children with developmental disabilities face substantial challenges in their daily lives, as they must respond to their child’s complex needs while simultaneously fulfilling their parental role. This responsibility demands substantial time, physical effort, and emotional investment [4]. Caregiving demands may adversely affect parents’ physical and psychological health and place strain on overall family functioning, partly through their influence on stress management, self-perception, and perceived social support [5,6].

The birth of a child with Cerebral Palsy often necessitates significant adjustments to family routines and may tigger emotional responses in parents, including denial, grief, and guilt. These reactions are closely related to the process of adapting to the child’s functional limitations and the long-term caregiving demand associated with the condition [7,8].

Elevated levels of parenting stress have been associated with impaired parenting practices, disruptions in parent-child relationships, and adverse outcomes for the children’s health and development [9,10]. Early identification and intervention targeting parenting stress—through family-centred care approaches—are therefore essential to support both child development and family well-being [11,12]. Moreover, higher levels of perceived stress have been linked to increased anxiety and reduced quality of life among caregivers [13].

Although qualitative research has explored on caregiving’ experiences across different populations, to the best of the authors’ knowledge, there is no qualitative study that explores the emotional experiences, stress management, challenges, and unmet needs of caregivers of children with motor/physical disabilities. Moreover, caregiving experiences and available support may vary substantially across healthcare systems and cultural contexts.

In this context, the present study aims to comprehensively investigate the experiences, psychological well-being, and unmet needs of caregivers of children with Cerebral Palsy in Spain through a sequential mixed-methods design. The study will fill an important gap in literature, providing context-specific evidence that can guide healthcare providers and policymakers in developing interventions and support strategies tailored to caregivers’ realities.

The Clinical Trial is registered at ClinicalTrials.org with the registration number NCT06912373, in April 2025, named “Experiences of Caregivers of Children with Cerebral Palsy (https://clinicaltrials.gov/study/NCT06912373?id=NCT06912373&rank=1)

## Materials and methods

To address the research question, the authors will use an **explanatory sequential mixed-methods** design consisting of three phases **(QUAN → Connection ◊ QUAL)**. The rationale for choosing this approach is that the analysis of the quantitative data will provide a general understanding of burden, stress and quality of life among caregivers of children with Cerebral Palsy. The subsequent analysis of the qualitative data will further explain the statistical results through an in-depth exploration of the experiences and needs of the participants [14].

A three-phase procedure will be used:

- QUANT phase: Quantitative data will be collected and analysed using three questionnaires, providing the authors with a comprehensive profile of participants’ stress levels, quality of life, and caregiver burden. This data will also enable the identification of specific subgroups that will be the primary focus of the subsequent qualitative phase, while informing the development of new research questions for a deeper exploration during this phase.- Connection phase: Firstly, based on the categories identified through the quantitative questionnaires, the content of the semi-structured interviews will be developed. Secondly, the results from the quantitative phase will inform the planning of the qualitative phase, including the selection of a potential subsample and the development of new questions that cannot be addressed through quantitative data.- QUAL phase: semi-structured personal interviews, based on the results of the quantitative data and followed by thematic analysis.

This study adopts an explanatory sequential mixed-methods design because the quantitative phase and the qualitative phase address complementary aims that cannot be achieved by either approach alone. The quantitative phase provides a population-level profile of caregiver burden, perceived stress, and quality of life, and examines associations among variables (e.g., sociodemographic factors, caregiving characteristics, and PedsQL-FIM subscales). These results will guide the development of the interview guide for the qualitative phase. In turn, the qualitative phase will generate in-depth explanations—mechanisms, contexts, and meanings—behind statistical patterns, allowing us to produce integrated, practice-relevant inferences. Integration will occur at three points; i) The results from the quantitative phase will help to plan the qualitative phase, including formulation of new questions ii) The development of the qualitative interview guide will be based on the categories identified in the questionnaires iii) The qualitative data will be integrated with the quantitative data to obtain a more comprehensive understanding of the quantitative results.

### Hypothesis and study objectives:.

Based on previous research on caregiving for children with Cerebral Palsy, we hypothesize that: (1) higher caregiver stress and burden will be associated with lower quality of life; (2) higher educational and income levels will be associated with lower burden and higher quality of life; and (3) the type or severity of Cerebral Palsy will show weaker associations with caregiver outcomes than psychosocial and contextual factors. These hypotheses are grounded in existing literature and will be examined in the regression models and subsequently elaborated in the qualitative phase, following the explanatory sequential mixed-methods design. Therefore, these hypotheses are considered hypothesis-generating and explanatory and will be further explored and contextualized through the qualitative phase. The overarching objective of this study is to generate an integrated understanding of the experiences, outcomes, and unmet needs of caregivers of children with Cerebral Palsy in Spain. Particularly, the quantitative analysis of caregiver burden, stress, and quality of life will provide the first objective; give a general profile, which will then inform and modify the development of the qualitative interview guide. The qualitative phase, second objective, will explore caregivers lived experiences, coping strategies, and perceived needs in depth, thereby expanding upon and contextualizing the quantitative findings. Stress, caregiver burden, and quality of life are conceptualized as co-primary constructs of interest, reflecting complementary and interconnected dimensions of the caregiving experience.

### Recruitment and data collection

#### Quantitative phase.

Before the recruitment begins, the principal investigator will present the project to the paediatric service of the Arnau de Vilanova University Hospital of Lleida (HUAV). During medical consultations, the paediatric service will inform eligible participants about the study. If the caregiver agrees to participate, they will give consent for the paediatric service to share their contact details with the research team. The investigators will then contact the participant to explain the project in detail, schedule a first meeting to sign the Informed Consent, and complete the initial questionnaires. Additionally, participants who sign the informed consent will be asked to provide their contact information for potential follow-up regarding the qualitative interview.

In the first meeting, participants who meet the inclusion criteria and have signed the informed consent will be directed to a study homepage hosted on the university’s website. This website will provide a link to a secure platform specifically designed for collecting research data (PedsQL-FIM, ZBI, PSS-14).

#### Sociodemographic data.

Participants’ sociodemographic data will include descriptive information such as age, sex, household income, among others.

#### Inclusion criteria.

- >18 years old- Being a caregiver of a child with Cerebral Palsy- Spanish/Catalan speaking- Willing to talk about their experiences and be audio/video-recorded.- Accept and sign the informed consent form

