#### Sample size considerations.

The quantitative sample size was estimated using GRANMO (estimation of a population mean). Assuming a 95% confidence level, a standard deviation of 21, based on Spanish normative data for the PedsQL-Family Impact Module [17]. Assuming an accessible finite hospital population of approximately 40 eligible caregivers and a precision of ±5 points on the 0–100 scale; the required sample is n = 26 completers. Allowing for an anticipated 15% attrition rate, the recruitment target is approximately 31 caregivers. This sample ensures estimation of the mean PedsQL-FIM score with adequate precision for the finite population. In addition, with n = 25–30 completers, two-tailed tests at α = 0.05 will have approximately 80% power to detect correlations of r = 0.50–0.54, providing sufficient power for moderate-to-large associations while acknowledging that smaller effects may be underpowered

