### Data analysis

#### Quantitative data.

The quantitative data will be analysed using descriptive statistics and frequency counts. Sociodemographic characteristics will be described. Descriptive statistics will be reported with means and standard deviations for continuous variables with normal distribution (age, child’s age, PSS-14, PedsQL-FIM, ZBI), or medians and interquartile ranges for variables without normal distribution. For categorical variables (sex, educational level, severity), both absolute and relative frequencies will be presented.

For the inferential analyses, Spearman’s correlations will be used to explore relationships among questionnaires (stress, burden, and quality of life) as well as to correlate caregiver outcomes (stress, burden, quality of life) across subgroups defined by sociodemographic variables (e.g., economic status, education level), child-related variables (e.g., severity of Cerebral Palsy, mobility), and caregiving factors (e.g., relation with the child). Primary analyses will use multivariable linear regression to model each caregiver outcome: (i) perceived stress (PSS-14), (ii) caregiver burden (ZBI), and (iii) quality of life (PedsQL-FIM total). Separate regression models are specified for stress, caregiver burden, and quality of life, consistent with their conceptualization as co-primary constructs, each examined to characterize different but interrelated dimensions of caregiver outcomes. Given the finite population constraints (approximately 40 eligible caregivers)), each model will include only the most relevant predictors (up to 2–3 per model), carefully selected on priori literature and clinical plausibility (e.g., socioeconomic status, caregiving duration, and child functional severity/mobility). This parsimonious approach reduces multiple comparisons and allows adjustment for potential confounders. Model assumptions, including linearity, normality of residuals, and homoscedasticity, will be evaluated using standard diagnostics such as residual plots and Shapiro-Wilk tests. If model assumptions are violated, data transformations or alternative statistical techniques will be considered. Results will be reported as standardized regression coefficients (β) with 95% confidence intervals. Analyses will be conducted using IBM SPSS Statistics v28 (or equivalent software) with significance level of α = 0.05 (two-tailed).

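### More than one caregiver of the same child can enrol, and the planned regressions make no allowance for it, so intervals for child- and household-level predictors may be too narrow

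*Protocol article*

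**What the plan says.** **Eligibility.** Of the five criteria under Inclusion criteria, the only one on the caregiving role is "Being a caregiver of a child with Cerebral Palsy". There is no restriction to one, or to the main, caregiver of a child.

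**Recruitment.** The Quantitative phase section describes an approach during the child's consultation and speaks of a single person: "If the caregiver agrees to participate, they will give consent for the paediatric service to share their contact details with the research team". It neither invites nor excludes a second caregiver.

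**Sample size.** Sample size considerations counts in caregivers throughout. The frame and precision are "approximately 40 eligible caregivers and a precision of ±5 points on the 0–100 scale", with "the required sample is n = 26 completers". It adds: "Allowing for an anticipated 15% attrition rate, the recruitment target is approximately 31 caregivers".

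**Analysis.** Under Data analysis, Quantitative data: "Primary analyses will use multivariable linear regression to model each caregiver outcome". The three outcomes are PSS-14, ZBI and PedsQL-FIM total, with two or three predictors each. The examples given are socioeconomic status, caregiving duration, and the child's functional severity or mobility. Standardized coefficients are reported with 95% confidence intervals. Spearman correlations are planned alongside, with no intervals mentioned. On checks: "Model assumptions, including linearity, normality of residuals, and homoscedasticity, will be evaluated using standard diagnostics", by residual plots and Shapiro-Wilk tests. Independence of observations and family membership are not mentioned.

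**The concern.** Two caregivers of one child have the same value for the child's severity and mobility, and the same or nearly the same socioeconomic status. Their stress, burden and quality-of-life scores may also be alike for reasons the model does not contain. Ordinary regression counts them as two independent pieces of information about a shared predictor, although they carry less than that. The standard error is then too small, the interval too narrow and the p-value too low.

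This bears on stated hypotheses. Hypothesis 2 concerns income and education, and hypothesis 3 compares severity with psychosocial and contextual factors. Both rest partly on predictors that are constant, or nearly so, within a family. Residual plots and a normality test would not reveal the problem, because paired residuals can look normal and homoscedastic. It also cannot be repaired later unless the data show which caregivers belong to the same child.

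**Working it through.** **1. The plan's own figures reproduce.** Inputs are from Sample size considerations: 95% confidence, SD 21, precision ±5, N = 40, attrition 15%.

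- Infinite population: n₀ = (1.96 × 21 / 5)² = 67.76.
- Finite population: n = 67.76 / (1 + 67.76/40) = 25.15, rounded up to 26.
- Attrition: 26 / 0.85 = 30.6, rounded up to 31.
- Power for a correlation (Fisher z), Φ(atanh(r)·√(n−3) − 1.96): 80.9% at r = 0.54, n = 25; 81.4% at r = 0.50, n = 30.

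There is no arithmetic error.

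**2. How many pairs could there be?** The protocol does not say. If 26 of the 40 complete at random as individuals, a given eligible pair is complete with probability (26 × 25)/(40 × 39) = 0.42. A frame containing 10 pairs then yields about 4 complete pairs. A frame of 20 couples yields about 8, and at least 26 − 20 = 6. Five to eight pairs therefore means that pairing is common in the frame. Fewer is quite possible, including none.

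**3. Effect on a predictor shared within the family.** With k pairs among 26 completers and the rest single, the design effect is 1 + (Σm²/Σm − 1) × ICC. Since Σm² = 4k + (26 − 2k) = 26 + 2k, this equals 1 + (k/13) × ICC. The true standard error exceeds the naive one by the square root of the design effect. Type I error is from 20,000 simulated data sets per cell, testing one family-constant predictor with no true effect. Ranges run over an assumed ICC of 0.3 to 0.7.

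| Pairs | Design effect | True SE exceeds naive by | Type I error (nominal 5%) |
|---|---|---|---|
| 0 | 1.00 | 0% | about 5% |
| 5 | 1.12–1.27 | 6–13% | 6.6–8.3% |
| 8 | 1.18–1.43 | 9–20% | 7.1–10.2% |
| 13 (all paired) | 1.30–1.70 | 14–30% | 9.0–14.3% |

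With 3 pairs the design effect is 1.07–1.16, and the true standard error is 3–8% larger than the naive one.

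**4. Effect on correlations among the questionnaires.** Stress, burden and quality of life differ between two caregivers of one child, so the inflation depends on the product of the two ICCs and is smaller. Simulated type I error of the Spearman test at n = 26, with both ICCs between 0.3 and 0.5, is 5.4–6.1% with 5 pairs, 5.6–6.6% with 8 and 6.1–7.6% if all are paired.

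**The case against.** **Nothing shows that pairs will enrol.** Recruitment is described in the singular, at a consultation. Relation to the child is an analysis variable, but it would vary with one caregiver per child too, so it is no evidence of pairs. This stands, and the point is therefore conditional. A reader might infer that the intervals are in fact too narrow; the protocol does not support that.

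**The ±5 precision.** A reader might also infer that the effective sample behind ±5 is overstated. That does not follow. When individuals are sampled from a finite frame of 40 caregivers, the variance of the mean is (1 − f)S²/n whatever the correlation within families. Drawing 26 of 40 from a frame of 20 couples gave a ratio of actual to formula variance of 1.00 at ICC 0 and at ICC 0.5. Precision would suffer only if couples joined or declined together, which the protocol does not suggest. The protocol also already says that the 40 are caregivers.

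**The outcomes are individual.** PSS-14 and ZBI measure the respondent's own stress and burden. In PedsQL-FIM only daily activities (3 items) and family relationships (5 items) are family dimensions by name. This is a fair reason to doubt a high ICC, and it is why a range is shown.

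**The list of checks is open, the article is condensed, and the study calls itself exploratory.** The exploratory label limits the consequence. It does not remove the point: the unit of eligibility and the primary model are both stated, and the named diagnostics would not trigger a search for an alternative method.

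**Conclusion.** The point holds in conditional form. The criteria admit several caregivers of one child, and the stated regressions make no allowance for that. If co-caregivers enrol and their outcomes are positively correlated after adjustment, inference on severity or mobility and on socioeconomic status is too optimistic. Under the assumed 5 to 8 pairs among 26 completers and ICC 0.3–0.7, the standard errors are 6–20% too low relative to the naive value, and type I error is about 7–10%. The effect is nil without pairs, smaller with few pairs, and smaller for correlations among the questionnaires. The all-paired row is an extreme without support in the text. For Spearman the effect is on p-values only, since no intervals are planned. The stated sample size is unaffected. This is a cheap improvement, not a flaw that undermines the study.

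**What to change.** Choose one of two routes in the protocol.

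1. **State in the inclusion criteria that one caregiver per child is enrolled**, and how that person is identified. This removes the issue, but caregivers then come only one per child, which may leave fewer to recruit from if the frame of about 40 includes pairs.
2. **Allow several caregivers per child and account for it.** Record a child or household identifier at enrolment. Use small-sample cluster-robust (CR2) standard errors by child in the three regressions; the correction is needed because there are few families. Obtain the Spearman p-values by a method that respects families, such as resampling by child. Add a sensitivity analysis with one caregiver per child.

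The second route costs one extra field, a different standard-error option and slightly wider intervals. If no pairs enrol, there is no clustering to correct. The identifier has to be captured at enrolment, because families may not be linkable once the data are anonymized.

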#### Qualitative phase.

The interview guide will be refined based on the results of the quantitative phase. Additionally, the findings from the quantitative questionnaires will inform the selection of participants for the interview phase. The interview will take place in the Faculty of Nursing and Physiotherapy of the University of Lleida. Interviews will be conducted in either Spanish or Catalan (participants’ choice) and will be recorded in audio or video, with participants’ previous consent. Once all questionnaire data has been analysed, a subgroup will be created based on the results obtained, which will be related to the categories identified in the PedsQL™ Family Impact Module [15] and the Zarit Burden Interview [16], both in their Spanish versions.

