#### Qualitative data.

Interviews will be audio- or video-recorded, transcribed verbatim, and analysed using a thematic analysis approach. Both deductive coding (guided by the quantitative findings and existing literature) and inductive coding (to capture emerging themes) will be applied. Codes will be organized into categories and higher-level themes to reflect caregivers lived experiences, coping strategies, and unmet needs. Two researchers will independently code a subset of transcripts to ensure inter-coder reliability, and discrepancies will be resolved through discussion until consensus is reached. Triangulation across researchers will further enhance validity. ATLAS.ti software will be used to manage and code the data [27,28]. It is anticipated a qualitative sample of approximately 10–15 participants, although data collection will continue until saturation is reached, defined as the point where no new relevant themes emerge. The approach will follow the Consolidated Criteria for Reporting Qualitative Research. This approach allows for analysis of the data with a set of expected themes informed by previous knowledge or research [29]. Integration of qualitative findings with quantitative results will be achieved through joint displays, side-by-side comparisons, and narrative weaving, allowing a comprehensive interpretation of caregiver outcomes and experiences. The first author will handle the interview analysis, while a different researcher will be involved in information triangulation to ensure the validity and reliability of the materials [30]. Subsequently, all authors will contribute to interpreting the data.

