### Limitations

The main limitations of this study include restricted generalizability, as it focuses on caregivers within the Spanish healthcare system, and potential self-report bias, as participants may overestimate or underestimate their stress levels and quality of life. Recruitment from a single hospital site may further limit the diversity of caregiver experiences represented, reducing external validity. However, this design ensures feasibility and methodological consistency while providing valuable context-specific insights. During the study, high caregiver workload may lead to participant dropout, affecting data collection, particularly in the qualitative phase. Discussing emotional burden may cause distress, influencing responses. Another limitation could be scheduling interviews, since it might be difficult due to caregivers’ unpredictable schedules, and response bias could arise if participants provide socially desirable rather than fully honest answers. These factors may impact data quality and the study’s overall conclusions. Future research should aim to replicate and extend the study across multiple sites to enhance generalizability.

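### Willingness to be interviewed and recorded is a condition for answering the questionnaires, which needlessly narrows a sample meant to describe about 40 caregivers and risks selection bias of unknown size and direction

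*Protocol article*

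**What the plan says.** The only eligibility list stands under Recruitment and data collection, between the Quantitative phase and Qualitative phase text. One of its items is "Willing to talk about their experiences and be audio/video-recorded". The Quantitative phase section makes the list a gate to the online platform that holds the three instruments: "participants who meet the inclusion criteria and have signed the informed consent will be directed to a study homepage".

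The interview is a later step for some participants:
- At enrolment, those who consent "will be asked to provide their contact information for potential follow-up regarding the qualitative interview" (Quantitative phase).
- Interviewees are chosen after the questionnaires have been analysed: "the findings from the quantitative questionnaires will inform the selection of participants for the interview phase" (Qualitative phase).
- Interviews "will be recorded in audio or video, with participants’ previous consent" (Qualitative phase).
- On numbers: "It is anticipated a qualitative sample of approximately 10–15 participants", with interviewing to continue until saturation (Qualitative data).

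Materials and methods gives the quantitative phase the task of profiling burden, stress and quality of life across the caregiver population. Sample size considerations rests on a finite population: "Assuming an accessible finite hospital population of approximately 40 eligible caregivers". It arrives at 26 completers and about 31 recruited.

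**The concern.** Nothing in the questionnaire phase is recorded, so consent to recording is not needed to answer it. As written, the rule removes from the descriptive estimates anyone who would complete the questionnaires but does not want to talk on record. Those caregivers supply no scores, so the analysis cannot repair the loss.

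Two things are at stake. The first is whom the means describe. If willingness to talk on record is related to stress, burden or quality of life, the means for enrolled caregivers differ from those of the whole caregiver group, and the finite-population interval does not reflect this. The second is recruitment. The target takes up most of a very small pool, and the 15% allowance covers attrition after recruitment, not refusal before it.

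**Working it through.** **Inputs from the protocol article.** Population about 40, SD 21, 95% confidence, precision ±5, 26 completers, 15% attrition, about 31 recruited (Sample size considerations); 10–15 interviews (Qualitative data).

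**The plan's own figures reproduce.**
- Without finite-population correction: n0 = (1.96 × 21 / 5)² = 67.76.
- With N = 40: n = 67.76 / (1 + 66.76/40) = 25.39, rounded up to 26.
- With 15% attrition: 26 / 0.85 = 30.6, rounded up to 31.
- Half-width at n = 26: 1.96 × (21/√26) × √(14/39) = 4.8 points. This is sampling error only.

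**How many meet a condition they will not use.** Of 31 enrolled, 10–15 interviewed is 32–48%, leaving 16–21 people (52–68%). Counted against 26 completers, 38–58% would be interviewed. Saturation could move these figures.

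**Room in the pool.** 31/40 = 77.5%, so 40 − 31 = 9 caregivers can be lost before enrolment for all reasons together. Suppose the 40 is counted before the willingness criterion, and let u be the unwilling share (assumed; not in the documents):

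| u | Willing | Completers if all willing enrol (× 0.85) |
|---|---|---|
| 10% | 36 | 30.6 |
| 20% | 32 | 27.2 |
| 22.5% | 31 | 26.4 |
| 30% | 28 | 23.8 |

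At 20%, 31 of 32 (97%) would have to enrol. At 30%, 31 cannot be reached and completers fall below 26.

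**Possible bias in the mean PedsQL-FIM.** The mean of all caregivers is (1 − u) × willing mean + u × unwilling mean. The willing mean therefore differs from it by u × (willing − unwilling). With assumed differences in units of the SD of 21, the absolute bias in points is:

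| u | 0.25 SD (5.25) | 0.5 SD (10.5) | 0.8 SD (16.8) |
|---|---|---|---|
| 10% | 0.5 | 1.1 | 1.7 |
| 20% | 1.1 | 2.1 | 3.4 |
| 30% | 1.6 | 3.2 | 5.0 |

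The sign depends on which group scores higher, and the documents do not say.

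**Effect on the interval.** Take the standard error as 4.84/1.96 = 2.47, holding n = 26 and N = 40 fixed for comparison. At a 0.5 SD difference, nominal 95% coverage falls to about 93% at u = 10% and about 86% at u = 20%. These are approximations. The same exercise cannot be done for ZBI and PSS-14, because no SD is given for them.

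**The case against.** **The link to the outcomes is inferred.** A reader might take the Limitations section as saying that burden and distress decide who enters. It does not. It says "high caregiver workload may lead to participant dropout, affecting data collection, particularly in the qualitative phase", which is loss after enrolment, and it treats distress as something that may affect answers. Refusal to be recorded could come from privacy concerns unrelated to the scores, and heavily burdened caregivers might be keener to talk. This stands: the documents do not show that the means are biased, or that they lean toward less burdened caregivers.

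**The 40 may already apply the criterion.** Sample size considerations calls these caregivers eligible. If that means meeting the full list, the pool does not shrink to 32 or 28 and the recruitment arithmetic above falls away. This also stands, and the text does not settle it. On that reading, however, the finite population consists of willing caregivers only, which is narrower than the profile promised in Materials and methods.

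**The rule keeps every score profile available for interview.** Interviewees are picked from questionnaire results, so nobody knows at enrolment who will be wanted. This argument is weak. A caregiver who will not be recorded is unavailable for interview under either rule, and moving the criterion removes no willing caregiver from the pool.

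**The study is exploratory.** The Discussion says so, and Limitations already concedes restricted generalizability. That lowers the stakes for hypothesis tests. It does not correct selection in a descriptive mean, which belongs to the first objective, and the limitations named (health system, single site, self-report) do not include selection by willingness to be recorded.

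**Conclusion.** The point holds as a needless restriction with a risk of selection bias. One list gates both phases, the questionnaires do not need the recording condition, and the interview stage already provides for consent. That much is in the text and needs no assumption.

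The size is conditional. With 10–30% unwilling and a difference of 0.25–0.8 SD, both assumed, the bias in the mean PedsQL-FIM is about 0.5–5.0 points in an unknown direction. That runs from negligible to as large as the stated precision of ±5. Recruitment is at risk only if the 40 is counted before the criterion.

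Three stronger conclusions are tempting but unsupported: that the means are biased toward better-off caregivers, that 31 cannot be recruited, and that the sample-size calculation is wrong. The first has no data behind it. The second depends on an unstated refusal rate and on what the 40 counts. The third is contradicted by the reproduction of 26 and 31.

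**What to change.** - Take the willingness and recording item out of entry to the questionnaire phase. Apply it only to caregivers invited to interview, with its own item on the consent form.
- State in Sample size considerations whether the 40 counts all caregivers of children with Cerebral Palsy at the hospital or only those who also meet this criterion.
- Report PedsQL-FIM, ZBI and PSS-14 scores by willingness to be interviewed, descriptively only. At 20% unwilling, 31 enrolled would split into about 6 and 25, too few for a test.
- If enrolment has already begun under the present rule, report how many caregivers were excluded for this reason and limit the population claim to willing caregivers.

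The cost is a small amendment to the criteria and consent form. The figures of 26 and 31 can stay if the 40 counts all caregivers; if it does not, N needs restating. The downside is that some of the 31 enrolled may decline interview, so the pool for purposive selection may be slightly smaller. Even at 30% unwilling, about 31 × 0.7 = 22 enrolled, or 26 × 0.7 = 18 completers, would remain for 10–15 interviews.
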